**Methods:**

The current study is a type 1 hybrid effectiveness-implementation trial to evaluate the impact of a proactive, opt-out tobacco treatment intervention on cessation outcomes and advance understanding of key barriers and facilitators of implementation processes. A total of 230 PWH who smoke will be recruited from an infectious diseases clinic at an academic medical center and will be randomized to receive (1) treatment as usual (TAU) or (2) Proactive Outreach with Medication Opt-out for Tobacco Treatment Engagement (PrOMOTE). Primary outcomes include: biochemically verified 7-day point prevalence abstinence (PPA) rates, continuous abstinence (Weeks 9–12), and the number of 24-hour quit attempts at the end of study treatment (Week 12). Secondary outcomes include: participant reach (proportion reached out of contact attempts), implementation fidelity (including number of prescriptions written), participant adherence to prescribed pharmacotherapy, acceptability (participant and provider satisfaction with intervention delivery and content), and perceived barriers.

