### Measures

Participants will complete a series of baseline measures at their first meeting by phone or through REDCap’s automated survey feature, including assessments of demographics, smoking behavior (including electronic cigarettes; behavioral risk factors (Behavioral Risk Factor Surveillance System [BRFSS][43]), alcohol (Alcohol Use Disorders Identification Test-C [AUDIT-C][44]) drug use and misuse (including marijuana[43]; Drug Abuse Screening Test-10 [DAST-10][45]), health, and HIV infection history. The Fagerström Test for Nicotine Dependence (FTND) will be completed at baseline to assess the severity of dependence on nicotine.[46–48] Participants will also verify their list of current medications, including ART regimen. Quantity and frequency estimates of tobacco, e-cigarettes, and alcohol use will be assessed using a Timeline Follow-Back Procedure starting 30 days prior to intake (repeated biweekly post-randomization until Week 12 and at the Week 24 follow-up).[49] Number of quit attempts and number of 24-hour quit attempts will be assessed using a similar calendar method biweekly from Weeks 2–12 and at the Week 24 follow-up. The Medication Adherence Questionnaire (MAQ) will be completed at baseline to assess each participant’s history of medication adherence.[50, 51].

 Participants will be assessed regarding their level of knowledge and attitudes toward varenicline and NRT at baseline and at Week 24. Additionally, every 2 weeks they will be asked if they received (PrOMOTE) or received/filled (TAU) their pharmacotherapy prescription (yes/no). The amount and frequency of smoking cessation pharmacotherapy used (per product) will be determined by utilizing the calendar method of data collection described above for tobacco use. Adherence to the smoking cessation pharmacotherapy regimen will also be calculated and will be defined as 80% or more of prescribed doses taken and will be calculated based on the self-report data from this assessment. Motivation and confidence to quit smoking will be assessed using a modification of the Contemplation Ladder[52, 53] which assesses readiness to quit in the next month.

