Secondary examination of implementation outcomes: Descriptive statistics will be used to characterize implementation outcomes at the participant and provider level on reach (number and type of participants randomized, the number of contacts made, answered, and completed), provider fidelity (number of contacts completed and number of prescriptions written), participant adherence (number of prescriptions filled), medication adherence (assessed as both a continuous variable of percentage of prescribed medication taken as well as binary yes/no ≥ 80% adherence achieved), and acceptability (average score on the AIM Survey). Implementation outcomes for PrOMOTE will be characterized, and contrasts will also be performed between randomized treatment study arms (PrOMOTE vs. TAU). Continuous and ordinal outcomes will be compared using a Wilcoxon Rank-Sum test statistic while categorical outcomes will be compared using a Pearson Chi-Square test statistic.

Qualitative analysis: Transcriptions of digital recordings of participant and provider interviews will be analyzed to identify key barriers and facilitators to implementation processes and outcomes using content analysis[68] with NVivo software[69] to identify, categorize, and contextualize theme patterns. Two independent coders will read and reread transcripts for all qualitative analyses, outlining and organizing key themes and sub-themes. Discrepancies will be discussed in team quality assurance meetings to develop consensus.

Data synthesis: After completing qualitative and quantitative data analyses independently, results will be synthesized to relate quantitative findings from surveys and tracking logs with qualitative data for the purpose of analysis and data triangulation.[70] Themes identified in qualitative data will be supplemented by patterns identified in quantitative findings to characterize provider and participant impressions.

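### The between-arm adherence contrast uses prescribed doses as its denominator, and having a prescription is a post-randomisation event selected differently in each arm

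*Protocol article*

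**What the plan says.** Under Measures, adherence to cessation medication "will be defined as 80% or more of prescribed doses taken and will be calculated based on the self-report data" from the use calendar. Under Planned analyses (the paragraph on implementation outcomes) the same quantity appears in a continuous form, "medication adherence (assessed as both a continuous variable of percentage of prescribed medication taken", and as a yes/no outcome at 80%. That paragraph adds that "contrasts will also be performed between randomized treatment study arms (PrOMOTE vs. TAU"), and names the tests: "Continuous and ordinal outcomes will be compared using a Wilcoxon Rank-Sum test statistic" and "categorical outcomes will be compared using a Pearson Chi-Square test statistic". No adjustment is mentioned. An earlier paragraph of the same section applies the intention-to-treat principle to all statistical analyses.

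Procedures describes how a prescription comes about. In TAU the clinic pharmacist can prescribe for a smoker who is interested in quitting, and the article itself calls this opt-in. In PrOMOTE every participant is proactively scheduled and medication is arranged unless declined. Someone who declines receives a motivational interview encouraging its use.

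Reach is worded in two ways. The abstract has "participant reach (proportion reached out of contact attempts"). Implementation outcomes and Planned analyses use counts of participants randomised and of contacts made, answered and completed.

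**The concern.** The denominator of the adherence measure is created by the process that the intervention is designed to change. Participants need not want to quit to be eligible, and randomisation is stratified on the motivation ladder (0–7 versus 8–10). Restricting to people with a prescription can undo that balance: TAU keeps those who asked for medication, while PrOMOTE keeps those who did not refuse it. If the two groups differ in how reliably they take medication, an unadjusted test compares different kinds of patient as well as different strategies.

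In a hybrid effectiveness-implementation trial these outcomes will inform decisions on dissemination. A significant adherence difference that comes only from who was prescribed could be read as a harm or a benefit of the opt-out strategy.

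**Working it through.** **The plan's own figure.** The article gives no planning figure for adherence. The number that matters here is 115 per arm, and it reproduces: 97 / (1 - 0.15) = 114.1, rounded up to 115. No stated figure is wrong.

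**Reading the definition.** For a participant with no prescription the continuous measure is 0 divided by 0. A Wilcoxon test can therefore include only those prescribed, unless a value is assigned to the others. The yes/no form could be kept on everyone by coding the unprescribed as no, but the article does not say so.

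**Illustration.** All rates here are assumptions.
- q = proportion prescribed in TAU (10–40%); r = proportion prescribed in PrOMOTE (60–90%).
- The q who would opt in are prescribed in either arm, and 60% of them reach the 80% threshold.
- The further r - q who are prescribed only under opt-out reach it in 30% of cases.
- Arm has no effect on any individual's adherence once prescribed.

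**Formulas.**
- Among those prescribed: TAU = 0.60; PrOMOTE = [q × 0.60 + (r - q) × 0.30] / r. The difference is -(1 - q/r) × (0.60 - 0.30).
- On all randomised, unprescribed counted as not adherent: TAU = q × 0.60; PrOMOTE = q × 0.60 + (r - q) × 0.30.

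**Worked case, q = 20%, r = 80%.** Those prescribed number 115 × 0.20 = 23 and 115 × 0.80 = 92. PrOMOTE among those prescribed is (0.12 + 0.18) / 0.80 = 37.5%, against 60.0% in TAU. On all randomised it is 0.12 + 0.18 = 30% against 12%.

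| Prescribed, TAU / PrOMOTE | Adherent among prescribed, TAU vs PrOMOTE | Difference (points) | Chance of p<0.05 | Adherent among all randomised | Difference (points) |
|---|---|---|---|---|---|
| 10% / 90% | 60.0% vs 33.3% | -26.7 | 43% | 6% vs 30% | +24 |
| 20% / 80% | 60.0% vs 37.5% | -22.5 | 50% | 12% vs 30% | +18 |
| 20% / 90% | 60.0% vs 36.7% | -23.3 | 54% | 12% vs 33% | +21 |
| 40% / 60% | 60.0% vs 50.0% | -10.0 | 18% | 24% vs 30% | +6 |

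The chances come from the normal approximation for two proportions, two-sided 5%. Over the twelve combinations examined (q = 10, 20, 30, 40%; r = 60, 80, 90%) the artefact among those prescribed runs from -10 to about -27 points, with an 18–54% chance of nominal significance. The sign on all randomised is opposite every time.

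**Dependence on the assumptions.** If the two groups adhered equally, the factor (0.60 - 0.30) would be zero and there would be no bias. If those prescribed only under opt-out adhered better, its sign would flip. If PrOMOTE's follow-up sessions raised adherence by 22.5 points in everyone prescribed there, the worked case would show 60.0% versus 60.0%. The contrast would then hide a real benefit, while all randomised would show 12% versus 0.80 × 60% = 48%.

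**The case against.** The strongest reply is that no sentence restricts the test to those prescribed. The contrasts are described as between randomised arms, intention to treat is stated for all analyses, and the coding of the unprescribed is the kind of detail an analysis plan supplies. This stands in part for the yes/no form. It does not rescue the continuous form, whose published definition has no value for the unprescribed. Denominator, tests and intention-to-treat statement are all fixed in the article and do not fit together.

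A second reply is that uptake is captured separately: prescriptions written and filled are planned contrasts, and TAU prescriptions from chart review are to be compared with PrOMOTE. That stands, and it limits the damage. It does not make the adherence contrast a randomised one. Adherence given a prescription is also a legitimate quantity of interest, which is a reason to keep it as description.

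Three stronger readings are tempting, and the documents do not support them.
- A reader might infer that the planned test will show PrOMOTE as worse. The rates are unknown, and PrOMOTE includes two further sessions that review adherence and side effects, which could push the other way.
- A reader might infer that reach is undefined in TAU. The ratio to contact attempts appears only in the abstract; the later sections use counts, and chart review of completed calls is planned in both arms. What remains is a difference in wording, and no statement of what counts as a contact attempt in TAU.
- A reader might see a fault in the arm-specific question, where "they will be asked if they received (PrOMOTE) or received/filled (TAU) their pharmacotherapy prescription (yes/no"). The wording broadly follows the delivery route, since PrOMOTE medication is mainly mailed, although pharmacy pick-up is allowed. It is a caveat on the filled-prescription contrast and no more.

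**Conclusion.** The point holds for adherence. As defined, the between-arm contrast conditions on a post-randomisation event that arises differently by arm. It is not a randomised comparison, and it conflicts with the article's own intention-to-treat statement. That conclusion needs no assumed rate.

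The size and direction of the bias do rest on assumptions. With 60% adherence in would-be opt-ins and 30% in those added by opt-out, a spurious difference of 10 to 27 points against PrOMOTE appears, and the sign reverses when all randomised are counted. Other assumptions would shrink, remove or flip it.

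For reach, only an inconsistency of definition between the abstract and the later sections is established. These are secondary outcomes that are also to be summarised descriptively. The primary abstinence analyses and the sample size are untouched. The change is worth making before adherence is compared by arm.

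**What to change.** 1. Make the between-arm adherence contrast on all randomised participants: the proportion taking at least 80% of a prescribed course, with the unprescribed counted as not adherent.
2. Present beside it the proportions prescribed and filled, with all randomised as denominator, so that uptake and adherence can be told apart.
3. Report the percentage of prescribed doses taken, among those prescribed, as within-arm description with the number prescribed shown, and without a between-arm test.
4. Use one definition of reach in the abstract and the analysis section, built on the counts with all randomised as denominator, and state what counts as a contact in TAU.

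The cost is mainly wording, because medication use comes from the calendars and TAU prescriptions from chart review. The statistical price is that the all-randomised measure combines uptake with adherence, which is why items 2 and 3 stay. The survey item on receiving or filling a prescription need not be changed: enrolment began in December 2021, and new wording would make the item inconsistent over time. The difference in wording should be noted when filled prescriptions are compared.

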## Discussion

This is the first study to test an opt-out, proactive tobacco treatment delivery approach with a focus on pharmacotherapy and behavioral support. The intervention is low-cost, has the potential to be highly scalable, and could be translatable to other ambulatory HIV clinic settings. This study will add to the literature on varenicline and NRT efficacy in PWH. Although varenicline and NRT have been independently shown to be effective for smoking cessation, there are very few studies evaluating these pharmacotherapies in PWH. Whether these approaches will improve quit rates for PWH in an ambulatory clinical setting is an empirical question. Of note, this trial can be conducted completely remotely using rigorous methods that have been well-established. An exploratory assessment of mediators and moderators of smoking cessation outcomes (i.e., nicotine dependence, medication adherence) is also an important feature of this study as these variables are understudied in PWH. We will examine implementation experiences concurrent with the trial to advance future dissemination of PrOMOTE.

## Data Availability

Not applicable.

## Abbreviations

ART: Antiretroviral Therapy.
PWH: People with HIV.
NRT: Nicotine Replacement Therapy (NRT).
TAU: Treatment as Usual.
